### Interventions

2.5.

#### Acceptance and commitment therapy (ACT)

2.5.1.

Study team members developed the ACT manual, which was informed by literature on the experiences of patients with advanced GI cancer and caregivers [1–3,10,35–37], the ACT model [20,22], prior ACT trials with cancer and other medical patients [21,24–26,38], and our clinical experience. Our team tested components of the intervention (e.g., mindfulness, values-based action) in our ACT trial targeting fatigue interference in patients with metastatic breast cancer [26]. Intervention components are summarized in Table 1. Based on the ACT model [20,22], the intervention addresses patient fatigue interference and caregiver burden through increasing psychological flexibility (see Fig. 1: Conceptual Model). Psychological flexibility is expected to increase through practicing mindfulness (e.g., meditations that encourage compassionate awareness of current internal experiences), learning adaptive coping strategies (e.g., acceptance, perspective-taking), identifying personal values (e.g., staying connected with family), and engaging in values-based actions. Participants set values-based action goals in the SMART format (Specific, Measurable, Achievable, Relevant, and Time-Bound).

Patients and caregivers jointly complete sessions 1 and 4–6 via speakerphone, whereas sessions 2 and 3 are separately delivered to patients and caregivers. We adapted ACT to the dyad by including joint mindfulness practices and a focus on their relationship during discussions. The therapist supports both participants in practicing compassionate acceptance of their own and each other’s thoughts, mitigating defensive reactions and fostering open communication. Individual sessions with patients and caregivers include discussing personal values. Additionally, the utility of attempts to avoid fatigue (for patients) or difficult thoughts and feelings about caregiving (for caregivers) is discussed. The emphasis in individual sessions is shifting from avoidance to pursuing values-based actions despite experiencing fatigue or caregiving burden.

During each session, patients complete three FSI items (i.e., average fatigue severity and fatigue interference with general activity and enjoyment of life) [29,30], and both patients and caregivers complete two Patient-Reported Outcomes Measurement Information System (PROMIS) depression items and two PROMIS anxiety items [39]. These assessments allow the therapist to monitor symptoms and may be examined in exploratory analyses. Each person’s home practice of ACT skills is also documented, and practice for the week ahead is discussed. One month after the 2-week follow-up, the same therapist holds a 30-min call with the dyad to reinforce ACT-based skills. Each person is sent handouts summarizing session topics and audio recordings that our team developed to guide mindfulness practices.

#### Education/support

2.5.2.

The education/support condition was tested in our pilot trial [21] and is comparable to controls in other cancer trials [40,41]. Dyads in this condition discuss their fatigue and other cancer-related concerns with a therapist providing reflective listening and empathic responses. The therapist directs dyads to resources for practical and health information and mental health services. The length of sessions and number and order of dyadic vs. individual sessions are the same as those for the ACT condition. Additionally, the same fatigue, depression, and anxiety assessments as those in the ACT condition are administered during each session [29,30,39]. Table 1 provides an overview of the education/support components. Sessions include an orientation to the patient’s hospital and treatment team, education about prevalent QoL concerns and symptoms experienced by patients with cancer and caregivers, and referrals to medical center and community resources for addressing these concerns. Therapists also describe resources for addressing financial concerns and methods of evaluating health information. One month after the 2-week follow-up, the same therapist holds a 30-min call with the dyad to reinforce concepts and encourage use of resources as needed. Each person receives handouts summarizing session topics and is asked to review them as homework. ACT concepts are not discussed.

#### Training and supervision of therapists

2.5.3.

Therapists are psychologists, social workers, certified life coaches through an International Coach Federation (ICF)-accredited program, or advanced doctoral students in clinical psychology with extensive training and experience delivering ACT or supportive counseling to medical populations. Each intervention is delivered by different therapists, and both conditions include therapists at diverse educational and career stages. Therapists received initial education in advanced GI cancer diagnosis and treatment, psychological distress, and either ACT or supportive counseling techniques. Initial training also included roleplays of sessions detailed in manuals. All sessions are digitally recorded, and fidelity monitors randomly select recordings to review for adherence to the manual using checklists developed in our pilot research. Additionally, seven items adapted from prior research [42–44] assess how consistently ACT therapists’ behaviors align with the ACT model. Individuals monitoring adherence have expertise in ACT or supportive counseling and were trained in fidelity monitoring. During weekly or biweekly supervision with therapists, clinical psychologists provide treatment adherence scores (number of required topics covered in each session/total number of fidelity criteria), and treatment fidelity and quality issues are discussed. Supervisor feedback is implemented in subsequent sessions.

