### Overview of study design

2.1.

This Phase II RCT tests the effects of telephone-based ACT on patient fatigue interference and caregiver burden in advanced GI cancer. We plan to enroll 244 patient-caregiver dyads over about four years. Dyads are randomized to six weekly 50-min telephone sessions of ACT or six weekly 50-min telephone sessions of education/support. Outcomes are assessed at baseline, 2 weeks post-intervention, and 3 months post-intervention (primary endpoint). Dyads in both conditions also complete a 30-min booster phone session one month after the 2-week follow-up. This trial is registered in clinicaltrials.gov (NCT06532877) and approved by the Indiana University Institutional Review Board.

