#### Analyses of potential covariates

3.1.2.

*T*-tests and chi-square analyses will be used to examine differences between study conditions on potential baseline covariates (e.g., demographics, medical factors). Any differences will be considered when interpreting results, and factors that differ between groups will be included as covariates in sensitivity analyses.

### Analysis for aim 1

3.2.

Linear mixed effects modeling (R lme4) [66] will be used to test the hypothesis that ACT will improve the primary outcomes of patient fatigue interference and caregiver burden as compared to education/support. The model for each outcome will include the main effects of time (as categorical) and condition (ACT vs. education/support) and the time-by-condition interaction. Time will be dummy coded using two dummy variables, with baseline as the reference group. A treatment effect will be evidenced by a significant time-by-condition interaction. If the treatment effect is significant, follow-up tests (R emmeans) [67] will be performed to examine group differences at each follow-up.

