We estimated the effect size based on the difference between study conditions on the primary outcomes of patient fatigue interference and caregiver burden at 3 months post-intervention. In our pilot RCT in advanced GI cancer, at 3 months we found a medium effect (*d* = −0.60) of condition (ACT vs. education/support) on patient fatigue interference and a small effect (*d* = −0.18) of condition on caregiver burden [21]. In contrast to our pilot, the current trial has a booster session to maintain ACT’s effects. Minimal clinically important differences (MCIDs) or clinically meaningful changes on the Fatigue Interference subscale of the FSI have been reported for cancer populations (range = 0.39–1.63) [68]. MCIDs in caregiver burden have yet to be determined. Estimates of treatment effects from pilots are imprecise [69,70]; thus, we examined results across relevant ACT trials and recommendations regarding MCIDs [71,72] to inform our power calculation. Although ACT has rarely been studied with cancer caregivers, it had a medium effect (*d* = −0.39) on dementia caregivers’ depressive symptoms – which are strongly correlated with caregiver burden [73] – relative to psycho-education at 6 months post-intervention [74]. Additionally, ACT had medium to large effects on mental health outcomes in a meta-analysis of RCTs for clinical populations [75]. In the absence of an established MCID for a self-report measure, a standardized effect size of 0.30–0.50 is recommended to estimate the MCID [71,72]. Thus, we estimate a moderate effect size of *d* = −0.40 for both primary outcomes. With *N* = 170 dyads at 3 months post-intervention (assuming 30 % attrition), we will have 85 % power (α = 0.05, two-tailed) to detect a Cohen’s *d* = −0.40 in a linear mixed model. The estimated attrition is based on our pilot data [21] and survival rates in advanced GI cancer [76].

### Analysis for aim 2

3.3.

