Linear mixed effects modeling (R lme4) [66] will be used to test the hypothesis that ACT will improve secondary outcomes as compared to education/support. For outcome measures that only patients or caregivers complete, models will include main effects of time (as categorical) and condition and the time-by-condition interaction. Treatment effects will be evidenced by a significant time-by-condition interaction. For outcomes reported by patients and caregivers, multilevel modeling for dyadic data will be used [77,78]. The model will include the main effects of time, condition, and social role (patient vs. caregiver) as well as all two and three-way interactions. The time x condition x role interaction will estimate the degree to which the treatment effect is different for patients and caregivers. The *p* values from the analyses will be adjusted using the Sidak approach to control for the familywise Type I error rate due to correlated multiple secondary outcomes. If treatment effects are significant, follow-up tests (R emmeans) [67] will be performed to examine group differences at each follow-up.

### Analysis for aim 3

3.4.

Cross-lagged panel models in Mplus [79] will be used to test the hypothesis that increases in psychological flexibility will mediate ACT’s effects on primary outcomes (patient fatigue interference and caregiver burden). Outcomes will be examined in separate models that include condition, the mediator (assessed at baseline and 2 weeks post-intervention), and the outcome at all time points. To evaluate model fit, we will use the comparative fit index (CFI) and the root mean square error of approximation (RMSEA), with CFI ≥0.95 and RMSEA ≤0.05 indicating close fit [80]. The indirect effect of condition on each outcome via psychological flexibility will be quantified using the product of the two relevant effects and tested using bootstrapped confidence intervals (CIs) accounting for nonnormality [81]. A total of 10,000 bootstrapped samples will be drawn, and the indirect effect will be considered statistically significant at *p* < .05 if the 95 % CI does not include zero.

### Analysis for aim 4

3.5.

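### Therapists are nested in condition, yet the models as written and the 85% power show no allowance for therapist clustering; if the therapist ICC exceeds zero, precision and power are overstated

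*Protocol article*

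**What the plan says.** Section 2.5.3 (Training and supervision of therapists) places the therapists within arms: "Each intervention is delivered by different therapists, and both conditions include therapists at diverse educational and career stages". They come from several professions and training levels. In section 2.5.1, one month after the first follow-up, "the same therapist holds a 30-min call with the dyad to reinforce ACT-based skills". Section 2.5.2 has the same arrangement for the control arm. The therapist relationship therefore lasts beyond the six weekly sessions.

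Section 3.2 (Analysis for aim 1) describes the primary analysis as follows: "The model for each outcome will include the main effects of time (as categorical) and condition (ACT vs. education/support) and the time-by-condition interaction". Section 3.3 (Analysis for aim 2) adds one level of clustering: "For outcomes reported by patients and caregivers, multilevel modeling for dyadic data will be used". Therapist does not appear in either section.

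On size, section 2.1 says: "We plan to enroll 244 patient-caregiver dyads over about four years". Section 3.2 then counts 170 "dyads at 3 months post-intervention (assuming 30 % attrition") and states "we will have 85 % power (α = 0.05, two-tailed) to detect" a standardized difference of 0.40 on either primary outcome. It gives no therapist count, therapist ICC, design effect or correlation between repeated measurements.

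**The concern.** Dyads who share a therapist may have outcomes more alike than dyads who do not. If each therapist treated dyads in both arms, a therapist's general effect would largely cancel from the comparison. Here it cannot, because each therapist belongs to one arm. The average therapist effect in the ACT arm minus that in the control arm is part of the estimated condition effect. Its sampling variance depends on the number of therapists, not only on the number of dyads.

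A model without a therapist term leaves that variance out of the standard error. Confidence intervals for both primary outcomes would then be too narrow, and chance differences between two groups of therapists would be declared significant more often than 5% of the time. A power figure that ignores it would be too high. Randomization is stratified by patient age and performance status (section 2.4), which does not address this.

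**Working it through.** **Inputs from the article.** 244 dyads randomized; 30% attrition; 170 dyads at 3 months; d = 0.40 in absolute value; two-sided alpha 0.05; power 85%. Equal allocation is implied by the block sizes of 2 and 4, so n = 85 per arm.

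**Assumptions not in the article.** k = 4, 6 or 10 therapists per arm with equal caseloads; therapist ICC of 0.01, 0.02 or 0.05 for the baseline-adjusted outcome.

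**Step 1: the plan's own figures.** Attrition reproduces: 244 × 0.70 = 170.8. For power, a plain two-sample comparison has expected z = 0.40 × √(85/2) = 2.61, and Φ(2.61 − 1.96) = 74%. The article refers to a linear mixed model, so use of the baseline measurement is reasonable to assume. With baseline adjustment the SD is multiplied by √(1 − r²). With r = 0.49 the factor is 0.872, z = 2.61/0.872 = 2.99, and power is Φ(1.03) = 85%. With change scores, r = 0.62 is needed. The article states no correlation, so 85% is attainable but cannot be confirmed. At r = 0.49 the 85% holds with a design effect of exactly 1.

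**Step 2: design effect.** With m = 85/k dyads per therapist, DE = 1 + (m − 1) × ICC. Example: k = 6, ICC 0.05: m = 14.2 and DE = 1 + 13.2 × 0.05 = 1.66. A standard error that ignores the therapist is too small by a factor √1.66 = 1.29.

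**Step 3: type I error without a therapist term**, 2 × [1 − Φ(1.96/√DE)]. Example: 1.96/1.29 = 1.52, giving 0.128.

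**Step 4: power once the clustering is counted.** Divide the z of 2.99 by √DE. Example: 2.99/1.29 = 2.32, and Φ(2.32 − 1.96) = 64%. The last column replaces the normal by a noncentral t with 2(k − 1) degrees of freedom.

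| Therapists per arm | ICC | DE | Type I error | Power, normal | Power, therapist df |
|---|---|---|---|---|---|
| 4 | 0.01 | 1.20 | 0.074 | 78% | 63% |
| 4 | 0.02 | 1.41 | 0.098 | 71% | 56% |
| 4 | 0.05 | 2.01 | 0.167 | 56% | 43% |
| 6 | 0.01 | 1.13 | 0.065 | 80% | 72% |
| 6 | 0.02 | 1.26 | 0.081 | 76% | 67% |
| 6 | 0.05 | 1.66 | 0.128 | 64% | 56% |
| 10 | 0.01 | 1.07 | 0.059 | 82% | 78% |
| 10 | 0.02 | 1.15 | 0.068 | 80% | 75% |
| 10 | 0.05 | 1.38 | 0.095 | 72% | 68% |

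**Step 5: simulation check** (86 per arm, r = 0.49, 4,000 null runs per setting). A baseline-adjusted comparison that ignores the therapist rejected in 4.3% (k = 4) and 4.9% (k = 6) of runs at ICC 0. At ICC 0.02 it rejected in 9.5% and 7.6%, and at ICC 0.05 in 17.8% and 13.0%. A t-test on therapist means stayed between 4.8% and 5.4% in these settings. Therapist-level inference therefore keeps the nominal level, and the excess appears only when the ICC is above zero.

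**The case against.** The strongest objection is that the article does not describe the random part of its models at all. Section 3.2 lists fixed effects only and does not name even the participant-level effect that three repeated measurements require. No one would conclude from this that repeated measurements are treated as independent. A reader might infer that the plan treats dyads sharing a therapist as independent. The article does not say so, and a fuller plan could include a therapist term. This stands, and it limits the point to the models as written.

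A reader might also infer that the 85% is wrong or that clustering was knowingly ignored. That is not shown either. A higher correlation with baseline would leave room for a design effect. At DE = 1.66, 85% would need (1 − r²) × 1.66 = 0.76, so r is about 0.74. The article states neither quantity. What stands is that no allowance is visible in a power statement that does list its sample size, effect size, alpha and attrition.

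A third tempting reading is that the type I error is inflated as a matter of fact. It is inflated only if the ICC exceeds zero and the therapist is left out. Section 2.5.3 describes manuals, role-play training, recorded sessions, fidelity checks and regular supervision. All of these may lower the ICC, and having varied career stages in both arms argues against a systematic imbalance in seniority. None of this sets the ICC to zero or measures it, and balance on average does not put therapist variance into the standard error.

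Finally, the table concerns a single comparison at 3 months, whereas the planned test is the time-by-condition interaction over two follow-ups. The percentages are illustrations, not error rates of the planned test. With few therapists the variance component may also be poorly estimated, which bears on the form of the remedy.

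**Conclusion.** The point holds in conditional form. The nesting of therapists in condition is stated, and the one-to-one link between therapist and dyad through the booster is strongly suggested. The models as written and the power statement show no allowance for it. If the therapist ICC is above zero, a model without a therapist term gives a standard error for the condition effect that is too small, and the stated power is too high.

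The direction follows from the design; the size does not. Over the assumed range, the approximate type I error runs from 5.9% (10 therapists per arm, ICC 0.01) to 16.7% (4 per arm, ICC 0.05). Power with the normal approximation runs from 82% down to 56%, given a baseline correlation of 0.49 chosen to match the stated 85%. The low end is of little consequence; the high end would weaken a claim of efficacy. The documents do not show where in this range the trial lies.

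**What to change.** 1. Record the therapist identifier for every dyad.
2. Prespecify, for Aims 1 and 2, a therapist random effect that acts on the follow-up measurements, with Satterthwaite or Kenward-Roger degrees of freedom. Baseline is measured before randomization (section 2.4), so the therapist cannot affect it. A therapist intercept shared by all three time points would largely cancel from the time-by-condition interaction and would not correct its standard error.
3. If there are too few therapists to estimate this variance, make the therapist-adjusted model a required sensitivity analysis, report it beside the primary result, and limit the efficacy claim accordingly. Fix this choice before unblinding.
4. Report the estimated therapist ICC for each primary outcome.
5. Restate power for the actual number of therapists over a range of ICCs, together with the correlation between repeated measurements on which it relies.

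The cost is analysis-plan wording and a data field the team should already hold. No extra participants or staff are needed to make these changes. The price is wider intervals and a less favourable stated power. The change makes the inference honest but does not recover power lost to clustering.

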### Retention

2.6.

Several strategies are used to increase study retention. All study personnel have been trained to clearly communicate study expectations to participants and to offer the option of completing follow-ups if they do not adhere to the intervention. Use of the telephone for all assessments and the intervention has resulted in strong retention in prior trials [21,45,46] and reduces barriers to participation for individuals with high symptom burden or low income. Text, phone, or email reminders are sent to participants before appointments. Each participant receives $40 in gift cards for participating in each of the three assessments, for a possible total of $120 in gift cards.

### Study measures and data collection schedule

2.7.

Study measures and the data collection schedule are shown in Table 2. REDCap is used to store study data. Patients and caregivers individually complete a 35-min baseline assessment and two, 30-min follow-up assessments conducted by blinded staff. All outcomes and mediators have evidence of internal consistency reliability and construct validity in cancer, general population, or caregiving samples [3,29,30,32,47–56].

#### Primary outcomes

2.7.1.

The primary outcome measure for patients is the 7-item Fatigue Interference subscale of the FSI [29,30]. Items evaluate the extent to which fatigue in the past week interfered with activities, mood, and cognition on 11-point scales (0 = no interference; 10 = extreme interference). The primary outcome measure for caregivers is the 12-item Zarit Burden Interview [32,47], which assesses personal strain and role strain due to caregiving on 5-point scales (0 = never; 4 = nearly always).

#### Secondary outcomes

2.7.2.

Patient *sleep interference* is assessed with the 8-item PROMIS sleep-related impairment measure, which evaluates the perceived interference of sleep problems with functioning [48,49]. Patient and caregiver e*ngagement in daily activities* is assessed with the 6-item PROMIS short-form measure of ability to participate in social roles and activities [50]. The items, which are reverse-coded, evaluate difficulty participating in social and recreational activities as well as usual work (including housework). Patient and caregiver *QoL* is measured with the 10-item PROMIS measure of global health, including physical, mental, and social well-being [51].

#### Mediators

2.7.3.

Patients and caregivers complete three measures of potential mediators. *Psychological flexibility,* as measured by the 7-item Acceptance and Action Questionnaire-II (AAQ-II) [52], is assessed as a hypothesized mediator of ACT’s effect on primary outcomes. The two core components of psychological flexibility are also evaluated as exploratory mediators. First, *mindfulness/acceptance* is assessed with the 10-item Cognitive and Affective Mindfulness Scale-Revised (CAMS-R) [53]. Items measure attention, present-focus, awareness, and acceptance/non-judgement. Second, *commitment/behavior change* is assessed with the 5-item Value Progress subscale of the Valuing Questionnaire [54]. This measure evaluates progress in living according to personal values.

